**LIST OF ABBREVIATIONS AND RELEVANT DEFINITIONS**

| **ABR** | **General Assessment and Registration form (ABR form), the application form that is required for submission to the accredited Ethics Committee; in Dutch: Algemeen Beoordelings- en Registratieformulier (ABR-formulier)** |
| --- | --- |
| **AE** | **Adverse Event** |
| **ANCOVA** | **Analysis of Covariance** |
| **ANOVA** | **Analysis of Variance** |
| **CA** | **Competent Authority** |
| **CCMO** | **Central Committee on Research Involving Human Subjects; in Dutch: Centrale Commissie Mensgebonden Onderzoek** |
| **DSMB**  **ECG** | **Data Safety Monitoring Board**  **Electrocardiography** |
| **EASD** | **European Association for the Study of Diabetes** |
| **EASL** | **European Association for the Study of the Liver** |
| **EASO** | **European Association for the Study of Obesity** |
| **EU** | **European Union** |
| **EudraC** | **European drug regulatory affairs Clinical Trials** |
| **GCP** | **Good Clinical Practice** |
| **GDPR** | **General Data Protection Regulation; in Dutch: Algemene Verordening Gegevensbescherming (AVG)** |
| **HCC** | **Hepatocellular carcinoma** |
| **IB** | **Investigator’s Brochure** |
| **IC** | **Informed Consent** |
| **METC**  **MRI**  **MRS**  **NAFL**  **NAFLD**  **NASH**  **REE** | **Medical research ethics committee (MREC); in Dutch: medisch-ethische toetsingscommissie (METC)**  **Magnetic Resonance Imaging**  **Magnetic Resonance Spectroscopy**  **Non-alcoholic Fatty Liver**  **Non-alcoholic Fatty Liver Disease**  **Non-alcoholic Steatohepatitis**  **Resting Energy Expenditure** |
| **(S)AE**  **SIBO** | **(Serious) Adverse Event**  **Small Intestinal Bacterial Overgrowth** |
| **Sponsor** | **The sponsor is the party that commissions the organisation or performance of the research, for example a pharmaceutical company, academic hospital, scientific organisation or investigator. A party that provides funding for a study but does not commission it is not regarded as the sponsor, but referred to as a subsidising party.** |
| **WMO** | **Medical Research Involving Human Subjects Act; in Dutch: Wet Medisch-wetenschappelijk Onderzoek met Mensen** |

**SUMMARY**

**Rationale:** Non-Alcoholic Fatty Liver Disease (NAFLD) is the most common cause of liver dysfunction with a global prevalence of 25 % which is accompanied by increasing obesity and obesity related metabolic diseases. NAFLD is defined as at least 5 % of fat in hepatocytes in absence of other hepatopathies. It covers a spectrum of different disease stages varying from non-alcoholic fatty liver disease (NAFL) to an advanced stage of the disease called non-alcoholic steatohepatitis (NASH). NASH is defined as steatosis with hepatocyte injury, inflammation and fibrosis while in NAFL only lipid accumulation is detected. Hepatocellular carcinoma (HCC) can develop at the fibrotic stage before any sign of symptoms of liver dysfunction. The end stage of the disease is cirrhosis which is an increasing cause of liver transplantations in the western world. There are currently no pharmacological treatment options to treat NAFLD or to prevent its progression to NASH, NAFL-related fibrosis or cirrhosis. Internationally recommended therapies include lifestyle intervention modifications targeting weight loss. Nevertheless, lifestyle interventions require a lot of resources. Additionally, weight loss as a clinical intervention is rather unsustainable. Exercise has been demonstrated to reduce (MRI based) hepatic lipid content in NAFLD patients without overall weight loss. However, the mechanism behind the effect of exercise independently of body weight change is unclear. There is a strong link between gut microbiota and the development of NAFLD. Additionally, exercise modulates gut microbiota. Thus, it can be suggested that the effects of exercise on NAFLD may not only be mediated through a physiological response to the liver, but through the gut microbiota and related metabolites. This study aims to investigate the clinical effect of exercise on molecular mechanisms involved in NAFLD and explore both interaction and relative contribution of liver, subcutaneous adipose tissue and muscle histology and gene expression in relation to glucose metabolism and gut microbiome composition. In addition to this we will study whether potential changes in the gut microbiota can be used to monitor exercise progression and predict the prognosis of NAFLD. Finally, potential biomarkers will also be searched for by transcriptomic analyses of liver, muscle and adipose tissue, and metabolomic analyses of blood, feces and urine.

**Objective**: We aim to study the effect of exercise on NAFLD (by analysing hepatic lipid content, liver histology, and gene expression). Furthermore, we aim to establish the role of exercise-mediated changes in gut microbiome in the reduction of severity of NAFLD and the relation with other metabolically involved organs including adipose tissue and muscle metabolism and glucose excursions. We thus aim to identify biomarkers of exercise effect on NAFLD state. These biomarkers comprise plasma and urine metabolites, gene expression of liver, muscle and adipose tissue, as well as gut microbial composition.

**Study design:** Intervention study.

**Study population:** In total 15 subjects aged 18-70 years of age with diagnosed NAFLD.

**Intervention (if applicable)**: High-intensity interval exercise training for 12 weeks.

**Main study parameters/endpoints:** The main study parameters are changes in NAFLD liver histology and gene expression in relation to oral and gut microbiota composition changes upon exercise. Second changes in other organs involved upon exercise driven metabolic fitness including subcutaneous adipose tissue and muscle gene expression (RNA-sequencing) and histology, in relation to glucose metabolism (freestyle libre) and metabolites in plasma and urine will be studied. Finally, the relative contribution to NAFLD and glucose metabolism of the different organs (liver, adipose tissue and muscle) upon exercise will be studied.

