A few recent studies investigated the transcriptome in NAFLD liver samples, they identified several genes associated with cirrhosis and alcohol metabolism, and suggested potential functional pathways and networks that were affected during different stages of NAFLD. They found some pathway perturbations in both NAFL and NASH that were associated with lipid metabolism and cell cycle control (Almanza et al., 2018; Gerhard et al., 2018; Suppli et al., 2019; Ye & Liu, 2015; Zhu et al., 2016) Even specific sets of genes have been identified in subgroups of NAFLD that can aid in discerning between high- and low-risk NAFLD related mortality (Lou et al., 2017; Moylan et al., 2014; Starmann et al., 2012) Moreover several studies have been conducted to analyse the transcriptomic effect of diet on the NAFLD liver, however the effect of exercise on hepatic gene expression is largely unknown (de Wit, Afman, Mensink, & Müller, 2012; Sales et al., 2018). The gene expression changes in muscle tissue following exercise intervention in NAFLD patients has not been analysed previously, though it is known that exercise does affect the muscle transcriptome (Damas et al., 2018; Hinkley et al,2017; Keller et al., 2011; Lundberg et al., 2016). This intervention study and the analysis of muscle transcriptome can thus be of great importance in understanding the underlying molecular mechanisms of the exercise effect on NAFLD. Previous exercise intervention studies have found an effect on NAFLD, however there is scant evidence of the underlying mechanisms of this effect. In addition to this, there are scarce clinical studies that have investigated the effect of exercise on the microbiome in relation to NAFLD (Porras et al., 2018). This study will investigate the clinical effects of high intensity exercise on NAFLD, and explore whether these effects are related to changes in gut microbiota composition. In addition to this we will study whether potential changes in the gut microbiota can be used to monitor exercise progression and predict the prognosis of NAFLD. Finally, potential biomarkers will also be searched for by transcriptomic analyses of muscle, adipose, and liver tissue, and metabolomics analyses of blood and urine.

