# STUDY DESIGN

This study is designed as an intervention study in which subjects will follow the 12-week exercise intervention. Subjects will receive instructions for a high-intensity aerobic interval training (HI) (described below). Dietary intake will remain unchanged. The first part of the study is conducted with 15 subjects. This is followed by an interim analysis and based on the results of this analysis, the intervention will be extended with another 15 subjects based on approval by the IRB. The study design is presented in figure 1.

Complementary study

Baseline

Mid-intervention

Final intervention

Interim analysis

Diagnosed NAFLD

(5.5 % > liver fat)

BMI < 40 kg/m^2^

18–70 years of age

n=15

Ergospirometry test

Anthropometrics

Food records

REE

Oral swab

Stool and urine samples

MRI and MRS

Blood samples

Liver, adipose tissue and muscle biopsies

Ergospirometry test

Anthropometrics

Food records

REE

Oral swab

Stool and urine samples

MRI and MRS

Blood samples

Liver, adipose tissue and muscle biopsies

Body weight

Food records

Oral swab

Stool samples

Blood samples

Exercise intervention – pilot study

Screening

Week 0

+/- 3 week

Identical to pilot study,

recruitment of

additional subjects

+/- 3 months

Continous glucose monitoring

Continous glucose monitoring

Week 12

+/- 3 week

Week 6

+/- 2 week

Figure 1 Overview of the study design with the main procedures that will be performed during the 12-week exercise intervention.

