## Sample size calculation

Based on hepatic PNPLA3 expression that is twice as high in steatosis patients compared to healthy obese subjects (Aragonès et al., 2016). To detect a 25% reduction in PNPLA2 expression upon 12 weeks exercise course, we expected to need a group sample size of 28 (2sided chi- square test with a desired alpha of 0.05 and a desired power of 0.8). Assuming around 10 % of dropouts in this trial, a final sample size of 30 is required. Based on the suggestions of the IRB we will start with inclusion of 15 subjects and study changes in liver gene RNAseq including PNPLA3 gene liver expression upon exercise (Aragonès et al., 2016). Based on those findings, we will validate our power calculation above and see if the number of 30 subjects is indeed needed.

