### Secondary study parameters/endpoints (if applicable)

Secondary study parameters include:

- Fecal and oral microbial composition, evaluated by metagenomic sequencing. This is based on oral and fecal sample at baseline, midway and endpoint.
- Metabolite quantification of plasma and urine samples. This is based on urine samples at baseline and endpoint, and blood samples at baseline, midway and endpoint.
- Gut motility in NAFLD patients. This is based on motility MRI analysis at baseline and endpoint.

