## Randomisation, blinding and treatment allocation

Not applicable.

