# STATISTICAL ANALYSIS

## Primary study parameter(s)

Statistical analyses will be performed by SPSS statistical analysis software. Normality of the data will be assessed by a Kolmogorov–Smirnov test. Data transformation will be done if the data is not normally distributed. The primary analyses of studied primary parameters will be performed between the baseline and endpoint intervention by analysis of one-sample t-test, or chi-square test. If the data is not normally distributed and data transformation is not possible, the Mann-Whitney test will be used. Further associations will be assessed with Pearson rank correlation test / Pearson chi-square test.

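### The Summary objective claims to establish the microbiome's role in reducing NAFLD severity, but one trained group analysed by association tests can show only that the two changes are related

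*Protocol*

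**What the plan says.** The aim appears at two strengths. The Summary's objective says "we aim to establish the role of exercise-mediated changes in gut microbiome in the reduction of severity of NAFLD". Section 1, closing the rationale, says the study will "explore whether these effects are related to changes in gut microbiota composition". The primary objective in section 2 concerns the effect of exercise on liver histology and genes in relation to microbiome composition, and the Summary's own endpoint paragraph uses the same kind of wording.

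The design is one group. Section 3: "This study is designed as an intervention study in which subjects will follow the 12-week exercise intervention". Section 6.2, on randomisation, blinding and allocation: "Not applicable". On numbers, section 3 says "The first part of the study is conducted with 15 subjects", with a further 15 conditional on an interim analysis. Section 4.4 says "we expected to need a group sample size of 28" before dropout, a figure derived for a change in gene expression.

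Liver biopsy and MRI/MRS are at baseline and endpoint (Summary, section 6.1.1). Section 6.1.2 says of microbial composition: "This is based on oral and fecal sample at baseline, midway and endpoint". Section 8.1 gives baseline-to-endpoint tests and then "Further associations will be assessed with Pearson rank correlation test" or a chi-square test. Section 8.2 applies the same methods to the microbiota data. Section 6.1.3 records body weight, body composition and diet as possible confounders, but section 8 names no adjustment.

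**The concern.** To establish a role for the microbiome, the study would have to separate three explanations of a correlation between microbiome change and liver change: the microbiome acts on the liver, the improving liver acts on the microbiome, or something else moves both. A correlation between two changes has the same value under all three. Since everyone trains, no contrast in the design separates them.

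Shared causes are plausible in this trial. Part of the weekly exercise is done at home (section 5.1, Table 1), so the amount done can vary. Subjects found to have NASH on the baseline biopsy are referred for dietary counselling (Summary), which could affect both gut and liver.

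What is at stake is the conclusion that may be drawn. Under the Summary's wording, a significant correlation in 15 to 30 uncontrolled subjects could be taken as evidence of a mechanism. Choosing a different correlation coefficient or correcting for multiplicity would not help, because the difficulty is one of direction and common cause.

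**Working it through.** **Step 1: what the design can separate.**

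| Needed to show mediation | Provided |
|---|---|
| A contrast in exercise | No: all subjects train (sections 3, 6.2) |
| Microbiome change shown to precede liver change | No: liver biopsy and MRI/MRS only at baseline and endpoint; a biopsy from the 12 months before screening may replace the baseline one (section 6.3.13) |
| Control of common causes | Some recorded (sections 6.1.3, 6.3.1, 6.3.2); no adjustment named in section 8 |

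A randomised control arm would identify the effect of exercise on each measure. It would not by itself identify the microbiome-to-liver path, because the mediator would still not be randomised.

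**Step 2: the test cannot tell direction.** Three models were simulated with the same true correlation of 0.5: microbiome to liver, liver to microbiome, and common cause. Each was significant in about 50% of trials at n=15 and 83% at n=30.

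**Step 3: error rate when the microbiome has no effect.** Inputs from the protocol are n=15 (section 3), n=28 (section 4.4) and two-sided 0.05 (the level in section 4.4, used here for the correlation). The strength of the shared cause is assumed, since the documents give no value.

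Let D be the shared cause, with microbiome change M = aD + √(1−a²)·e₁ and liver change L = aD + √(1−a²)·e₂, where e₁ and e₂ are independent. There is no path between M and L, so their correlation is a × a = a². The test is t = r√((n−2)/(1−r²)). It is significant when |r| exceeds 0.514 at n=15 or 0.374 at n=28. Results from 100,000 simulated trials per cell:

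| a | a² | n=15 | n=28 |
|---|---|---|---|
| 0 | 0 | 5% | 5% |
| 0.3 | 0.09 | 6% | 7% |
| 0.5 | 0.25 | 14% | 25% |
| 0.6 | 0.36 | 27% | 48% |
| 0.7 | 0.49 | 48% | 78% |

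These are rates for a single microbial feature.

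**Step 4: what adjustment achieves.** Suppose D is recorded with reliability R. The partial correlation of M and L given the recorded value is then a²(1−R)/(1−a²R). At a=0.7 and R=0.6 this is 0.49 × 0.4 / (1 − 0.294) = 0.28, down from 0.49. Significance rates after adjustment, for a from 0.3 to 0.7:

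| Reliability R (assumed) | n=15 | n=28 |
|---|---|---|
| 1.0 | 5% | 5% |
| 0.8 | 5% to 8% | 5% to 13% |
| 0.6 | 5% to 16% | 5% to 29% |

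**Step 5: the week-6 stool sample.** Using microbiome change to week 6 as predictor of liver change to week 12 gave the same error as the 12-week change under a shared cause acting from the start: 15% and 48% at n=15, 27% and 81% at n=30, for a = 0.5 and 0.7.

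**The case against.** The best defence is that the strong wording is one sentence in a Summary. The formal objectives claim only a relation, the rationale is hedged and itself calls for more randomised trials of exercise and microbiota, and section 6.7 describes a pilot of 15. This stands as a limit on scope: the protocol as a whole does not promise mediation. It does not remove the conflict between that sentence and the design.

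The choice of covariates may be left to a statistical analysis plan. That is fair for the details. But no such plan can add a comparator or a mid-study liver measurement.

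Four stronger readings are tempting, and the documents do not support them.

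- A reader might infer that an inert microbiome would often be credited. That depends on the assumed strength of the shared cause: at 0.3 the rate is 6% to 7%. Supervised sessions (section 5.1) and withdrawal of subjects who do not follow instructions (section 6.4.1) may also narrow the variation in exercise done.
- A reader might infer that the week-6 sample is being wasted and would solve the problem. Section 8.1 does not exclude it, and step 5 shows that it would not remove a shared cause. Nor would it fix the time order, because the liver change still runs from week 0.
- A reader might infer that confounding was ignored. Section 6.1.3 names weight, body composition and diet as possible confounders. What is missing is their use in section 8.
- A reader might infer that a significant correlation will be reported as a proven mechanism. The protocol states no such rule.

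**Conclusion.** The concern holds as a mismatch between the Summary objective and what the design can deliver. That part needs no assumption: a single trained group, with the liver assessed before and after and variables linked by association tests, cannot establish mediation or its direction.

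The size is conditional. For one inert feature and a shared cause correlating 0.3 to 0.7 with both changes, the false-association rate is about 6% to 48% at n=15 and 7% to 78% at n=28, against 5%. Only the first 15 subjects are committed, so the n=15 figures are the ones to read first. The upper ends require a strong shared cause and should not be read as expected rates.

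The change is worth making because it costs little and alters what may be concluded from a significant result.

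**What to change.** 1. Reword the Summary objective so that it aims to explore whether changes in the gut microbiome are associated with changes in NAFLD severity, in line with sections 1 and 2.
2. State in section 8 that a significant association does not establish mediation or direction.
3. Assess the microbiome-liver association adjusted for exercise actually done, from the activity monitor (section 6.3.1), and for dietary change, from the intake lists (sections 6.1.3 and 6.3.2). The protocol does not list session attendance or work completed as recorded data, so the adjustment should not rely on them.
4. Adjust for weight change only in a sensitivity analysis, because weight may lie on the pathway and adjusting could remove part of the effect being sought.
5. Do not present the week-6 sample as the remedy.

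The cost is a weaker claim and a few degrees of freedom: with two covariates at n=15, residual degrees of freedom fall from 15 − 2 = 13 to 15 − 4 = 11. Some confounding will remain because exercise done is measured imperfectly; at an assumed reliability of 0.6 the error rate could still reach about 16% at n=15 and 29% at n=28. No new data collection is needed.

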**Nature and extent of the burden and risks associated with participation, benefit and group relatedness:**

This study is a continuation of our previous intervention studies aiming to study underlying mechanisms of gut microbiota in liver gene expression in NALFD-NASH subjects (MASH study 2013_207) and our study on the role of microbiota on muscle gene expression and glucose metabolism (APPETITE study 2014_084). Oral microbiota is studied by taking an oral swab of the upper front teeth rime in overnight fasted subjects that refrained from tooth brushing that morning (FATMED study 2016_117). Moreover, we currently are building a large prospective cohort of patients with NAFLD-NASH to follow the natural course of (liver biopsy proven) changes in NAFLD-NASH between baseline and after 5 years (2017_311). Participants will be recruited from our outpatient clinics. An ultrasound or transient electrography will be performed to establish hepatic steatosis, if they do not already have an existing diagnosis. All subjects will in total have six site study visits, and total 21 hours in 12 weeks. At each visit we will collect blood and fecal samples. In addition, body weight will be measured at each visit. Other anthropometrics including height and waist circumference will be screened at baseline. At the baseline (first) and endpoint (final) visit we will collect (ultrasound guided) liver, muscle and subcutaneous adipose tissue biopsies, and Magnetic Resonance Imaging (MRI) and Magnetic Resonance Spectroscopy (MRS) will be performed. During these two visits, bioelectrical impedance will be conducted to screen body composition and resting energy expenditure (REE) will be determined. Also, ergospirometry test will be performed to determine the intensity of the individually prescribed training program and the efficacy of the exercise intervention. Exercise habits will be assessed by a questionnaire for the entire 12-week intervention period. Additionally, an objective physical activity monitoring will be performed through the intervention. Subjects will also fill in online questionnaires regarding their food intake for one week prior to each visit. Glucose monitoring will be conducted for 4 weeks during the intervention, 2 weeks at the baseline and 2 weeks before the end of the intervention to screen the effect of the exercise on glucose metabolism.

Our study participants will be referred to the AMC intervention radiology department for liver biopsy to assess NAFLD histology severity and gene expression (RNA sequencing) in liver tissue. As an experienced interventional radiologist will perform the liver biopsy ultrasound-guided, the risk (comprising mostly bleeding from the biopsy site) of complications will be very low (<0.1 %). Moreover, local hemostasis after the procedure will be observed and bleeding disorders or anticoagulant therapy are an exclusion criterion. Based on our previous experience, we might encounter ~ 1 patients with a complication (most likely small bleeding) in our entire study. Despite ample efforts to establish non-invasive methods in small groups of NAFLD/NASH patients over the last decade, a liver biopsy is still the gold standard for discerning between NAFLD and NASH and provides possibility to study gene expression. NASH refers to an advanced state of NAFLD which is characterised by hepatocyte injury, inflammation and fibrosis. When participants are found to have NASH in their baseline liver biopsy, they will be referred to our outpatient clinic for clinical follow-up and dietary counselling.

